### Setting

This study is set on the Sunshine Coast of Queensland, Australia. In Australia, the current percentage of people aged 65 years and over accounts for around 14% of the population [1]. On the Sunshine Coast this percentage is expected to increase to 17% by 2031 [36]. The study will be conducted in the Nambour General Hospital, situated in the Sunshine Coast and Hospital Health Service (SCHHS). Nambour General Hospital is one of four public hospitals in the SCHHS. NGH is the base hospital containing 373 beds and the three secondary hospitals have a combined total of approximately 531 beds. All four hospitals have an ED where both adults and children are treated. The study ED has an annual presentation of 52,410 patients; 18% of whom are over the age of 70 years [36]. Locating the research in the SCHHS will provide evidence of the effectiveness and feasibility of this MOC in a regional setting.

### Intervention

GEDI is a nurse-led, physician-championed innovative MOC that aims to reduce frail older person living in the community or RACF ED length of stay and streamline service delivery by maximising the provision of care during the patient’s ED journey. GEDI clinical nurses (CN) have a minimum of five years post registration experience and specialist expertise and/or education in both emergency nursing and care of the older person. Their role focuses on case-managing frail older persons living in the community or RACF in the ED facilitating rapid access and coordination of care through ED, hospital and community services.

There are 2.4 full time equivalent (FTE) GEDI CNs and a 0.8 FTE Clinical Nurse Consultant (CNC) employed by the ED. They cover the ED from 0700 to 1730 Monday to Friday and 0700 to 1530 on weekends. The GEDI CNC oversees the CN role, providing education, leadership, managerial oversight of the service and clinical support where needed. An ED physician provides medical leadership and together with the CNC they are responsible for research and administration.

In the ED, the GEDI team will provide early, rapid, targeted geriatric assessment of frail older persons living in the community or RACF presenting to the ED and, through careful inter-facility and interdisciplinary, management and planning, aim to prevent unnecessary admissions to hospital. In addition, the GEDI CNs provide a single point of contact for ED and RACF staff who may be having difficulty managing an older person with an acute illness. Table 1 outlines the elements included in the GEDI roles. The importance of the ED clinical experience required for the GEDI role relates to the need for GEDI CNs to optimise communication; multitask within a chaotic, fast-paced clinical environment; and be familiar with the staff, clinical pathways and protocols.

**Table 1 Tab1:** GEDI team responsibilities

GEDI Clinical Nurse Consultant	GEDI Clinical Nurse	GEDI Physician
Clinical responsibilities		
▪ Collaborative partnership with physician-champion to develop evidenced based guidelines specific to the needs of the geriatric patients and clinicians in the ED	▪ Works collaboratively with all ED staff	▪ Clinical resource and expert in geriatric emergency medicine
▪ Develops and maintains enhanced communication strategies related to ED staff, RACF staff, Nurse Practitioner (NP), community services, paramedic staff and general medical practitioners (GPs).	▪ Enhanced communication by providing a dedicated single point of contact within the ED for RACF staff, NP, community services, paramedics and GPs to obtain support and advice regarding optimal care and management of acutely unwell or injured frail older person or RACF resident	▪ Facilitates interdisciplinary discussions and establishes clinical hospital wide networks
▪ Develops and upskills CNs in use of rapid assessment of frail older persons or RACF residents	▪ Rapid assessment and management of frail older persons or RACF resident including nurse initiated analgesia and investigations	▪ Identify information to be sourced by the GEDI CN relevant to ED medical officers
▪ Develops evidence based clinical care algorithms for common problems experienced by RACF residents within the ED	▪ Provides evidence based clinical care for older persons in the ED in collaboration with the primary nurse	▪ Provide education for emergency staff, promoting informed decision making and best practice
▪ Provision of a consultative service for patient centred care of the frail older person or RACF resident within the ED	▪ Provision of a consultative service for patient centred care of the frail older person or RACF resident within the ED	
▪ Develops systems and upskills CNs to undertake direct referral to Geriatricians and rapid consultation pathways with other medical service streams	▪ Direct referral to Geriatricians and rapid consultation pathways with other medical service streams	
▪ Develops systems to facilitate pre-hospital communication with the RACF, GP, NP and Ambulance service, facilitating appropriate transfer decision making and early arrival triage	▪ Pre-hospital communication with the RACF, GP, NP and Ambulance service, facilitating appropriate transfer decision making and early arrival triage	
	▪ Liaison with hospital acute-care substitution services such as the Hospital in The Home and palliative care services	
Administrative responsibilities		
▪ Collaborative partnership with physician-champion to manage the GEDI team and GEDI CN portfolios	▪ Facilitation of discharge back to place of residence or admission – i.e. appropriate disposition planning	▪ Implement MOC and promote care of the older persons in ED
▪ In collaboration with GEDI Physician and university partners coordinate a program of research focused on the care of older persons in ED	▪ Ensuring discharge summaries are provided to all care providers e.g. GPs, RACF, primary carers, community services following acute ED care to allow seamless transition of care	▪ Create and edit clinical pathways and guidelines for best practice i.e. Delirium management
▪ Coordinate the aged care component of the ED staff development program in consultation with GEDI CNs and ED Nurse Educator	▪ Provide education for ED staff in evidence based care of the frail older person or RACF resident	▪ Leader in change management and lean thinking strategies
▪ Coordinate NP clinical practicum in the ED for NP candidates specialising in care of the frail older person or RACF resident to enhance skill base and knowledge of the ED setting. Skills obtained are translated into practice within the aged care service setting.	▪ Facilitate education/clinical exposure in the ED for NP candidates specialising in care of the frail older person or RACF resident to enhance skill base and knowledge of the ED setting.	▪ Negotiation of resource use in the ED
	▪ Establishment of rapid, direct referral pathways to specialised geriatric and palliative care departments	▪ Champion the GEDI model in strategic planning with senior staff and hospital administration
		▪ Collaborate and maintain research relationships
		▪ Participate in research and program audits
		▪ Administrator of GEDI team and budget
		▪ Collaborate with national and international geriatric focus groups
		▪ Liaise with other program directors/coordinators

### Study design

Pragmatism will provide the philosophical paradigm for this mixed model evaluation research. This philosophical paradigm allows the researcher to focus on “what works” and provides solutions for problems utilising methods that best meet their needs and purpose [37]. The design will be underpinned by Donabedian’s structure, process and outcome evaluation of healthcare framework [38].

The three studies included in this protocol will aim to answer the following evaluative research questions:What is the effect of the introduction of the GEDI MOC on the outcomes of frail older persons living in the community or RACF who present to ED? (Outcomes include: rates of ED representation within 72 h and 28 days, mortality, ED and hospital LoS, time to referral and hospital admission rates).What structures and processes are required to deliver the GEDI MOC?Specifically:What are the experiences of staff in regards to the processes of the GEDI MOC?What processes pertaining to the GEDI MOC have affected the day to day operation of the ED, and how?What are the residents’ and carers’ experiences of the GEDI MOC?
What is the effect of the GEDI MOC on hospital and health service delivery costs?Specifically:What is the effect of the introduction of the GEDI MOC on per patient cost associated with ED and hospitalisation?What is the effect of the introduction of the GEDI MOC on preventing the costs associated with avoidable inpatient admissions?

#### Study 1: Pre-post comparison of GEDI MOC in the ED

Study one is a quasi-experiment comparing outcomes for patients seen by the GEDI team to historical controls. As with all quasi-experiments, the disadvantage lies in the internal validity and risk of bias and this experiment will predominantly be affected by selection and historical control bias. Further to the selection bias and given the time difference between the pre and post intervention groups, events within the ED may influence the observed effects and lead to historical bias. Throughout the intervention a record will be made of any process or system changes that occurred within the ED during the GEDI team’s implementation [39]. These will be incorporated into the analysis.

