**Methods:**

The Geriatric Emergency Department Intervention research project consists of three interrelated studies within a program evaluation design. The research comprises of a structure, process and outcome framework to ascertain the overall utility of such a program. The first study is a pre-post comparison of the Geriatric Emergency Department Intervention in the emergency department, comparing the patient-level outcomes before and after service introduction using a quasi-experimental design with historical controls. The second study is a descriptive qualitative study of the structures and processes required for the operation of the Geriatric Emergency Department Intervention and clinician and patient satisfaction with service models. The third study is an economic evaluation of the Geriatric Emergency Department Intervention model of care.

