## Methods/design

### Study aims

The aims of the Geriatric Emergency Department Intervention (GEDI) MOC evaluative research project are to:Test the efficacy of the GEDI MOC by comparing the outcomes of all people aged 70 years or older who presented to a South East Queensland ED before the implementation of the GEDI MOC with those in the 12 months following implementation. Outcomes measured will be: rates of ED representation within 72 h and 28 days, mortality, ED and hospital LoS, time to referral, time to disposition and hospital admission rates;Describe and explore the structures and processes required for the effective delivery of the GEDI MOC;Conduct an economic evaluation of the GEDI MOC.

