##### Samples

The study sample comprises frail older persons living in the community or RACF presenting to Nambour General Hospital ED during two time-periods:(i)Time 1: 1^st^ January to 31^st^ December 2012: prior to development of any aspect of GEDI MOC, and(ii)Time 2: GEDI MOC implementation: 1^st^ September 2015 to 31^st^ August 2016

The gap between these two time-periods was when the GEDI MOC was developing, partially staffed and supported and was, therefore, not operating at an optimal level.

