##### Data collection

Data extraction will occur retrospectively via medical records audit of coded state based Health Service databases, namely Emergency Department Information Service (EDIS; Healthcare Group, CSC)® and Hospital Based Corporate Information System (HBCIS; iSoft). SCHHS Health Statistics unit provides linking of the EDIS, HBCIS and financial data providing raw data on all presentations to the ED and those admitted to hospital. The raw data will subsequently be manually cleaned to identify RACF residents based on their home addresses. This is important as RACFs often have independent living community residents at their facilities who needed to be excluded from this cohort. Independent variables that will be used to describe the sample and used to build multivariable models for outcomes are:Demographics - Age, Sex, postcodeDate and time of presentationClinical diagnosis – reason for presentation and ICD-10 code/categorySeen by GEDI team – Yes/NoAustralasian Triage Score [40]Adult Deterioration Detection System Score [41]Next of Kin/Substitute decision maker/Enduring Power of Attorney detailsTime to referral from ED arrivalTime to disposition from ED arrival

Outcome variables collected will be:Disposition - discharged home, moved to short stay area, admitted, diedED LoS – in minutesHospital LoS – in daysAll cause in-hospital mortality within 30 days of ED presentationED Re-presentations in 72 h and 28 daysTime to ED re-presentation within 28 days

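### Study 1 defines its comparison in three incompatible ways, and the version that compares GEDI-seen patients with historical controls carries a selection bias that the planned adjustment does not address

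*Protocol article*

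**What the plan says.** The protocol article describes the Study 1 comparison in several places.

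- **Study aims:** the first aim is stated as "comparing the outcomes of all people aged 70 years or older who presented to a South East Queensland ED before the implementation", set against those presenting in the 12 months afterwards. The criterion is age alone.
- **Study design, research question 1:** the effect is sought on the "outcomes of frail older persons living in the community or RACF who present to ED".
- **Samples:** "The study sample comprises frail older persons living in the community or RACF presenting to Nambour General Hospital ED during two time-periods". This section gives no age limit and no definition of frailty.
- **Study 1, opening statement:** "Study one is a quasi-experiment comparing outcomes for patients seen by the GEDI team to historical controls".
- **Abstract, Methods:** a period comparison, "comparing the patient-level outcomes before and after service introduction using a quasi-experimental design with historical controls".

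The Study 1 Data collection section lists a yes/no indicator of GEDI contact among the independent variables that describe the sample and build the multivariable models. The same section says the linked databases are "providing raw data on all presentations to the ED and those admitted to hospital". The only step it describes for identifying a cohort is finding RACF residents by home address.

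The Data analysis section adjusts all models for gender, age, triage score, season, day of the week and time of presentation, and adds a linear date trend.

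**The concern.** The three descriptions are different estimands. The first is the effect of introducing the service on everyone aged 70 or older. The second is that effect in a frail subgroup. The third is a contrast between patients the team actually saw and an earlier cohort. The same data can give materially different answers to each, and nothing in the article says which one is the headline result.

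The third version also has a validity problem. GEDI contact is a post-arrival event that depends on whom the nurses judge to need them and on whether the patient is still in the department. Frailty and time in the ED are both plausibly related to admission, length of stay, mortality and re-presentation. A difference between seen patients and 2012 controls could therefore reflect who was seen rather than what the team did.

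**Working it through.** **1. Can each population be formed alike in both periods?**

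- *All aged 70 or older:* yes. Age is a listed variable, and the extract covers all presentations in each period.
- *Frail older persons:* not from the listed variables. No frailty instrument or score is among them. The triage and deterioration scores measure acute severity.
- *Seen by GEDI:* no. Time 1 is "prior to development of any aspect of GEDI MOC", so no 2012 patient could have been seen.

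A yes/no contact variable also implies that the Time 2 sample includes patients who were not seen. That conflicts with the design statement.

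**2. How far apart can the populations be?** From the Intervention section, weekly cover is 5 × 10.5 h + 2 × 8.5 h = 69.5 h, and 69.5/168 = 41.4%. From the Setting section, 0.18 × 52,410 ≈ 9,434 presentations a year are by people over 70. If arrivals were even over the week (an assumption; daytime arrivals are probably more common), 9,434 × 0.414 ≈ 3,900 would arrive during cover. The seen group may therefore be a minority of the first aim's population.

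**3. Spurious admission difference with no true effect.** The article states no effect size, power or sample size for Study 1, so there is no figure to reproduce. Assumptions:

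- admission is 60% in both periods (the Background's approximate literature figure, assumed to hold for this ED);
- the seen share is s;
- the admission risk ratio, seen to not seen, is r and reflects selection only.

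Then p(unseen) = 0.60/(s·r + 1 − s), p(seen) = r·p(unseen), and the spurious difference is p(seen) − 0.60.

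| s | r | p(seen) | difference, points | 95% CI |
|---|---|---|---|---|
| 0.20 | 0.8 | 0.500 | -10.0 | -12.5 to -7.5 |
| 0.20 | 0.9 | 0.551 | -4.9 | -7.4 to -2.4 |
| 0.20 | 1.1 | 0.647 | +4.7 | +2.3 to +7.1 |
| 0.20 | 1.2 | 0.692 | +9.2 | +6.9 to +11.5 |
| 0.414 | 0.8 | 0.523 | -7.7 | -9.5 to -5.8 |
| 0.414 | 0.9 | 0.563 | -3.7 | -5.5 to -1.8 |
| 0.414 | 1.1 | 0.634 | +3.4 | +1.6 to +5.2 |
| 0.414 | 1.2 | 0.665 | +6.5 | +4.7 to +8.3 |

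The intervals use an unpooled standard error with s × 9,434 seen patients and 9,434 controls. Every interval excludes zero. The differences are unadjusted; age and triage would probably absorb some of them.

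**4. Spurious ED length-of-stay difference with no true effect.** Assumptions: lognormal length of stay with mean 257 minutes, exponential wait for contact with mean w, and a patient is seen only if the wait is shorter than the stay. None of these inputs is in the documents. With length of stay L, the chance of being seen is 1 − exp(−L/w). The excess in mean length of stay among seen patients, in minutes, is:

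| log-SD of length of stay | w = 30 | w = 60 | w = 120 |
|---|---|---|---|
| 0.4 | 0.4 | 3.5 | 11.6 |
| 0.7 | 4.1 | 14.8 | 35.9 |
| 0.8 | 6.8 | 21.0 | 47.2 |

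In this model the excess runs from about 0 to 47 minutes, and its size depends on the assumed wait and spread.

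**5. Dilution under the all-comer contrast.** A true effect of 5 points confined to seen patients gives s × 5 points overall: 0.20 × 5 = 1.0 and 0.414 × 5 = 2.1.

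**The case against.** The best defence is that the article is less divided than it looks. Its wording about frail people in the community or residential care recurs throughout as a stock label, the first aim supplies the operational age rule, and the Abstract and the economic study both describe a period comparison. On that reading only the Study 1 design statement is out of line. That is plausible, but a reader cannot be sure of it, and correcting the wording would then cost almost nothing. A condensed article may leave the measurement of frailty to the full protocol. It should not state the comparison groups incompatibly.

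The article also concedes that selection and historical-control bias will predominate. That disclosure counts in its favour. However, the stated measures (a record of system changes, a date trend and a seasonal term) deal with change over time, not with whom the nurses saw.

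Four stronger readings are tempting, and the documents do not support them.

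- *Limited cover leaves arrival hour as an uncontrolled confounder.* Day of the week and time of presentation are already in every model.
- *The bias is known to be large and in one direction.* The inputs are assumed. The intervention is described as early and rapid, and with short waits the length-of-stay excess is close to nil (under 2 minutes at a mean wait of 15 minutes for log-SDs up to 0.8).
- *The 2012 controls are unselected.* This is an inference, because Samples describes both periods in the same terms. What can be said is that no listed variable could select them comparably.
- *Including GEDI contact turns the period coefficient into the effect in unseen patients.* That would follow if both terms were in one model, but the Data analysis section states no such model.

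**Conclusion.** The concern stands as an internal contradiction about the main comparison of Study 1, together with a selection bias that is built into one of the stated versions. The contradiction rests on the text alone.

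The bias argument rests on two facts in the document. No 2012 patient could have had GEDI contact, and the adjustment set contains no measure of frailty or of remaining in the ED until contact. Its size and sign cannot be determined from the documents. The ranges of about -10 to +9 points for admission and about 0 to 47 minutes for length of stay show only that assumed, modest selection could produce differences large enough to be mistaken for an effect. They are not estimates for this ED.

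**What to change.** Reconcile the Study aims, research question 1, the Study 1 design statement, Samples and Data collection on one primary contrast: all presentations by persons aged 70 or older in Time 1 versus Time 2, regardless of GEDI contact. This is the first aim's population, and it can be identified by the same rule in both periods.

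Keep the GEDI-contact variable out of the primary outcome models. Report it as reach, or use it in a clearly labelled secondary analysis that handles the selection explicitly. One option is to define exposure by arrival during staffed hours, which is known at arrival in both periods. The report should then note that patients who arrive shortly before cover starts and are still present would be misclassified.

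No new data are needed, since the extract already covers all presentations. The real cost is the dilution worked out above: a 5-point effect in seen patients would appear as about 1 to 2 points. The interpretation should say that the primary result is the effect of introducing the service, not the effect in those it reached.

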##### Samples

The study sample comprises frail older persons living in the community or RACF presenting to Nambour General Hospital ED during two time-periods:(i)Time 1: 1^st^ January to 31^st^ December 2012: prior to development of any aspect of GEDI MOC, and(ii)Time 2: GEDI MOC implementation: 1^st^ September 2015 to 31^st^ August 2016

The gap between these two time-periods was when the GEDI MOC was developing, partially staffed and supported and was, therefore, not operating at an optimal level.

##### Data collection

Data extraction will occur retrospectively via medical records audit of coded state based Health Service databases, namely Emergency Department Information Service (EDIS; Healthcare Group, CSC)® and Hospital Based Corporate Information System (HBCIS; iSoft). SCHHS Health Statistics unit provides linking of the EDIS, HBCIS and financial data providing raw data on all presentations to the ED and those admitted to hospital. The raw data will subsequently be manually cleaned to identify RACF residents based on their home addresses. This is important as RACFs often have independent living community residents at their facilities who needed to be excluded from this cohort. Independent variables that will be used to describe the sample and used to build multivariable models for outcomes are:Demographics - Age, Sex, postcodeDate and time of presentationClinical diagnosis – reason for presentation and ICD-10 code/categorySeen by GEDI team – Yes/NoAustralasian Triage Score [40]Adult Deterioration Detection System Score [41]Next of Kin/Substitute decision maker/Enduring Power of Attorney detailsTime to referral from ED arrivalTime to disposition from ED arrival

Outcome variables collected will be:Disposition - discharged home, moved to short stay area, admitted, diedED LoS – in minutesHospital LoS – in daysAll cause in-hospital mortality within 30 days of ED presentationED Re-presentations in 72 h and 28 daysTime to ED re-presentation within 28 days

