## Background

Across the developed and developing world the population is ageing. In Australia it is predicted that, compared to 2005 the proportion of the population over 65 years of age will increase from 13% to 24%, by 2036 [1]. With this increase, the demand on Emergency Department (ED) services by older persons living in the community or in residential aged care facilities (RACF) will increase [1–3]. A systematic review of 27 studies from around the world has demonstrated that the rate of transfer to EDs from RACFs is 0.1–1.5 transfers per RACF bed/year [4].

As a result of this ageing of the population it is imperative that the health care system develop safe models of care (MOC) that span both the community and hospital health care sectors. While the ED is uniquely designed to care for the critically ill or injured, it is often a suboptimal environment for the provision of care to the frail, older person [5, 6]. Prior research shows that older persons who develop an acute illness or who have an acute exacerbation of a chronic condition, have complex medical needs and the doctors and nurses who manage their initial care in the ED often have limited experience in geriatric medicine [7, 8]. Several studies have shown that this situation leads to: under-triage; higher rates of admission; delayed and fragmented care; longer stays in the ED; and unnecessary investigations and invasive interventions [9–19]. For patients from RACFs this is particularly true. During admission to hospital, patients from RACFs are at high risk of complications such as delirium, urosepsis, falls and death [20–22]. Patients from RACFs who develop an acute illness or an exacerbation of a chronic condition also suffer high rates of re-presentation to the ED and subsequent re-admission to hospital [2, 10, 12, 14].

Several studies indicate that a large percentage of frail older persons living in the community or RACFs express a preference for treatment in their home if appropriate [23, 24]. Despite this, approximately 60% of ED presentations lead to hospital admission [25, 26]. In an attempt to keep frail older persons at their place of residence during an acute illness, several MOC have been designed and tested. Broadly, the different MOC are divided into those that: i) provide in-home care or outreach of services from one service to another [12, 24, 27, 28]; ii) provide prioritisation or geriatric focused care in the ED [29–32]; or iii) support or enhance primary care [28, 33].

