##### Data analysis

Descriptive statistics will be used to describe the intervention and control groups including frequencies, percentages, appropriate measures of central tendency and distribution. We will use survival analysis to jointly model length of stay and disposition, with the four destinations as competing risks. We will use survival analysis for ED representations with out-of-hospital mortality as a competing risk. All models will adjust for the patient level factors of gender, age, triage score, season, day of the week and time of presentation. Pre-post designs are vulnerable to confounding by other changes over time that may be attributed to the intervention [39]. To control for this, we will include a linear trend (based on date) in all models to account for gradual changes that are not captured in the individual variables, e.g., experience of healthcare workforce. We will also adjust for season using a sinusoid with an annual cycle to control for the winter peak in morbidity [42]. The survival analyses will use Cox models and we will check the proportional hazards assumption. The models’ residuals will be checked for outliers and correlation over time. We will calculate Cook’s influential statistic and examine relatively large outliers. We will calculate the variance inflation factor and remove variables with a score above five on the basis that they are co-linear. The key outcome will be the mean effect of the intervention together with 95% confidence intervals. The results will be reported using the Strengthening the Reporting of Observational Studies in Epidemiology (STROBE) guidelines [43].

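### Study 1 has no rule for several ED presentations by one person; if presentations are the rows, the 95% intervals will tend to be too narrow

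*Protocol article*

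**What the plan says.** The Study 1 Data collection section describes linkage of the ED, inpatient and financial systems, "providing raw data on all presentations to the ED and those admitted to hospital". The outcomes listed there mostly belong to a visit: disposition, ED length of stay in minutes, death in hospital within 30 days of the presentation, and return to the ED within 72 hours or 28 days. The Study aims section instead describes the population as persons: "comparing the outcomes of all people aged 70 years or older who presented to a South East Queensland ED".

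The Study 1 Data analysis section sets out two survival models. For stay and disposition: "We will use survival analysis to jointly model length of stay and disposition, with the four destinations as competing risks". For returns: "We will use survival analysis for ED representations with out-of-hospital mortality as a competing risk". It adds "The survival analyses will use Cox models and we will check the proportional hazards assumption". On adjustment it says "All models will adjust for the patient level factors of gender, age, triage score, season, day of the week and time of presentation"; triage score, day and time vary from visit to visit. All models also carry a linear date trend and an annual sinusoid, and variables with a variance inflation factor (VIF) above five are to be removed. The one check on dependence is that "residuals will be checked for outliers and correlation over time". The key result is the mean intervention effect with its 95% confidence interval.

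The Background says that patients from residential aged care "also suffer high rates of re-presentation to the ED and subsequent re-admission to hospital".

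**The concern.** An extract of all presentations, analysed for visit-level outcomes, has several rows for anyone who attends more than once. Two visits by one person share frailty, comorbidity and home circumstances, so their outcomes are likely to be correlated. A Cox model with its ordinary model-based variance treats the rows as independent. Checking residuals for correlation over time is not aimed at two visits by one person that may be weeks or months apart.

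The exposure is the calendar period, so all of a person's visits within a period share the same exposure. For a simple pre-post contrast, positive within-person correlation then makes the true variance larger than the model reports. The interval at stake is the one that the article calls its key outcome.

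One row per person would also be a legitimate design, but it needs a rule for choosing the index presentation. Neither the Samples section nor the Data collection section gives one. The cleaning that is described only identifies residents of aged care facilities.

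**Working it through.** **There is no figure to reproduce.** The article gives no sample size, event count, visits per person or ICC. The only derivable number is volume. The Setting section gives 52,410 presentations a year, 18% of them by people over 70: 52,410 × 0.18 = 9,434 a year, or about 18,868 over two 12-month periods at constant volume.

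**Step 1. Simple pre-post contrast, no date trend.** Assumed inputs: mean presentations per person m = 1.4 to 2.0; within-person ICC = 0.1 to 0.3; geometric numbers of visits per person.
- Size-weighted mean cluster: m_w = 2m − 1.
- Design effect: DE = 1 + (m_w − 1) × ICC.
- True SE / naive SE = √DE.
- Coverage of a nominal 95% interval = 2Φ(1.96/√DE) − 1.

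| m | ICC | m_w | DE | SE ratio | Coverage |
|---|---|---|---|---|---|
| 1.4 | 0.1 | 1.8 | 1.08 | 1.04 | 94.1% |
| 1.4 | 0.3 | 1.8 | 1.24 | 1.11 | 92.2% |
| 2.0 | 0.1 | 3.0 | 1.20 | 1.10 | 92.6% |
| 2.0 | 0.3 | 3.0 | 1.60 | 1.27 | 87.9% |

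A ratio of 1.27 means that the true SE is 27% larger than the naive SE. Equivalently, the naive SE is 1 − 1/1.265 = 21% too small. At an ICC of 0 the ratio is 1 and there is no problem.

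**Step 2. Cox model for 28-day return, no date trend.** Simulation with about 19,000 presentation rows, a gamma frailty per person, no true period effect, and either none or 30% of persons eligible in both periods (60 runs per setting). The person-clustered robust SE divided by the naive SE was:
- frailty variance 0.5: 1.03 to 1.04;
- frailty variance 1: 1.08 to 1.09;
- frailty variance 2: 1.17 to 1.22;
- frailty variance 3: 1.26 to 1.34.

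Mean presentations per person-year ran from 1.55 to 2.23 across these settings. The range overlaps that of Step 1.

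**Step 3. Effect of the planned date trend.** With the trend in the model, the period effect is identified mainly from dates within each year. These differ between one person's visits, so much of the shared person effect cancels. In a linear model with the Step 1 inputs (20 runs per setting), the robust/naive ratio was:
- no trend: 1.04 to 1.26;
- trend and sinusoid, visits spread over the year: 1.00;
- trend and sinusoid, visits moderately bunched within person: 1.02 to 1.10;
- trend and sinusoid, visits tightly bunched within person: 1.03 to 1.19.

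A logistic simulation of 28-day return with visits spread over the year agrees: 0.98 to 1.03 with the trend and sinusoid, 1.05 to 1.25 without.

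**Step 4. Would the trend stay in the model?** The periods in the Samples section each last 366 days and their midpoints lie 1,339 days apart. With presentations spread evenly:
- date variance within period: 366²/12 = 11,163;
- date variance between periods: (1,339/2)² = 448,230;
- share of date variance explained by period: 448,230/459,393 = 97.6%;
- VIF = 459,393/11,163 = about 41.

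Adding the sinusoid cannot lower this. Period and trend both exceed the limit of five. Removing the period indicator would leave no effect to estimate, so the rule in practice removes the trend and brings back the Step 1 and Step 2 figures.

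**The case against.** The strongest reply is that the article nowhere says that each presentation is a row. The quoted phrase describes the raw extract, the aims speak of people, and one index visit per person is not excluded. Nor does the article name a variance estimator, and an article may leave that to an analysis plan. This stands in part: the unit is an inference and the conclusion must stay conditional. It does not dispose of the point. The outcomes and most covariates are visit-level and no index rule is given. The section is specific about the model class, covariates, trend, season, influence statistics, a collinearity cut-off and one form of dependence, yet it leaves out the form that these data most obviously have.

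A second reply is that the planned date trend largely removes the problem. Step 3 confirms this when visits are spread over the year. It fails when visits are bunched, as returns within 28 days are, or when the collinearity rule drops the trend.

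Third, every input beyond volume is assumed, and the Background remark on frequent returns is qualitative and concerns aged care residents only. That stands.

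A reader might also infer that a return visit is counted twice, or that the return outcome suffers most. Neither is supported. A return is the event of one row and the time origin of the next, as in ordinary gap-time analysis. No comparison across outcomes was made, and the simulated figures for returns overlap the generic range.

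**Conclusion.** The point holds in conditional form. The article does not name its unit of analysis and has no provision for repeat presentations by one person. If presentations are the rows, the variance is model-based and outcomes are positively correlated within person, the 95% intervals for the pre-post effect will tend to be too narrow.

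Under the assumed 1.4 to 2.0 presentations per person and ICC of 0.1 to 0.3, the true SE is about 4% to 27% larger than the naive SE if the date trend is out of the model, and from nil to about 19% larger if it stays in. At the low end this hardly matters; at the high end a nominal 95% interval covers about 88%.

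The stronger reading, that the plan prescribes independent rows and its intervals are certainly too narrow for every outcome, goes beyond the text. Confidence is moderate. The change is worth making because it costs so little.

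**What to change.** State in the Study 1 Data analysis section that the presentation is the unit of analysis. Use a robust (sandwich) variance clustered on the linked patient identifier in all Cox models, including each competing-risk component, and in the Study 3 cost models. Add one sensitivity analysis restricted to each person's first presentation in each period.

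The cost is one option in the model code, one further analysis and slightly wider intervals. An identifier that links a person's visits is already needed to find returns to the ED. Because the Study 3 costing data are de-identified, a coded person key must be kept in that file. If within-person correlation turns out to be negligible, the intervals will barely change.
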